#### **4.1.5 Study Reporting Period for Solicited symptoms, AEs, MA-LRIs, and SNMCs**

The reporting period for solicited symptoms and unsolicited AEs is the period immediately following each study vaccine administration through 28 days after each dose. AEs must be followed until resolution or stabilization, even if this extends beyond the 28-day post-dosing reporting period (for the purpose of obtaining a stop date for the event).

The reporting period for SNMCs is the period immediately following initial study vaccine administration through 365 days post randomization.

The reporting period for MA-LRIs is the period immediately following initial study vaccine administration through 365 days post randomization. An MA-LRI is also an **immediately reportable event** (see Section 4.5).

#### **4.1.6 Study Reporting Period for Enhanced Disease Surveillance**

Although there is no evidence that vaccination with any live attenuated RSV candidates predisposes subjects to increased severity of disease with subsequent RSV infections, the goal of this surveillance is to evaluate the link between any severe morbidity/hospitalization and RSV infections. To monitor for possible enhanced RSV disease, laboratory confirmation of the presence or absence of RSV in respiratory secretions will be collected for all MA-LRIs. All MA-LRIs will be assessed for severity according to [APPENDIX B](#). The overall grading of a MA-LRI should be the highest degree of severity assigned among all of the components of the respiratory event detailed in APPENDIX B. Nasal samples will be collected by the investigator within 24 hours (or as soon as possible) after onset of the event and will be analyzed at a central laboratory for respiratory virus identification. The reporting period for enhanced disease surveillance is the period immediately following study vaccine administration through 365 days post randomization. In addition, information regarding oxygenation status, supplemental oxygen requirements and specific drug treatment will be collected, as well as any other concurrent respiratory illness present at the time of the diagnosis of the event.

In the unlikely event that a statistically significant difference between vaccine group and placebo group in the rate of RSV-related hospitalization or death at the end of the study follow-up period (365 days after randomization in a cohort) is observed, then the protocol and informed consent form will be amended to continue to follow enrolled subjects through an additional RSV season. For the purpose of surveillance, the following definition for RSV enhanced disease will be used: a clinically significant increase in rates of RSV-related hospitalization or death in vaccinees

compared with placebo subjects. To qualify as an RSV-related hospitalization or death, either wild-type RSV must have been identified in a clinical specimen OR a valid negative result for RSV testing was not available from a clinical specimen obtained during the window from 2 days prior to onset of symptoms to 5 days after onset of symptoms (ie, in the absence of a confirmed negative culture, events are analyzed as if associated with shedding of wild-type RSV).

#### 4.1.7 Recording of Solicited symptoms, AEs, MA-LRIs and SNMCs

AEs, MA-LRIs and SNMCs will be reported on the CRF using a recognized medical term or diagnosis that accurately reflects the event. Solicited symptoms will be reported on the CRF using the pre-defined terms in this protocol and will be assessed by severity. AEs and SAEs will be assessed by the investigator for severity, relationship to study vaccine, possible etiologies, and whether the event meets criteria as a Grade 3/4 AE, SAE, or a MA-LRI and therefore requires immediate notification of the sponsor (Sections, 4.2.3, 4.2.4 and 4.2.5). SNMCs will be assessed for relationship to study vaccine. See Sections 4.3 and 4.4 regarding guidelines for assessment of severity and relationship, respectively, Section 4.2.1 for the definition of SAEs, and Section 4.1.3 for the definition of MA-LRIs. If an AE has not resolved at the end of the study reporting period it will be documented as ongoing on the corresponding CRF. If an AE or solicited symptom evolves into a condition that becomes “serious” it will be reported on the Serious Adverse Event Report Form. Information recorded on the Adverse Event Case Report Form must be substantiated in the source documents.

## 4.2 Serious Adverse Events

### 4.2.1 Definition of Serious Adverse Events

A Serious Adverse Event (SAE) is any adverse event that results in any of the following outcomes:

- Death
- Life-threatening\*
- Inpatient hospitalization or prolongation of existing hospitalization‡
- Persistent or significant disability or incapacity†
- Congenital anomaly/birth defect (in the offspring of a subject)
- An important medical event that may not result in death, threaten life or require hospitalization may be considered a serious adverse event when, **based upon appropriate medical judgment**, it may jeopardize the subject and may require medical or surgical intervention to prevent one of the outcomes listed above. Examples of such medical events include allergic bronchospasm requiring intensive treatment in an emergency room

or at home, blood dyscrasias or convulsions that do not result in inpatient hospitalization, or the development of drug dependency or drug abuse.

\*Life threatening: An adverse event is life threatening if the subject was at risk of death at the time of the event; it does not refer to an event which hypothetically might have caused death if it were more severe.

‡Hospitalization: An inpatient hospitalization will be defined as an admission (or emergency room visit) for a period greater than 24 hours. Hospitalization for either elective surgery related to a pre-existing condition which did not increase in severity or frequency following initiation of the study or for routine clinical procedures¶ (including hospitalization for “social” reasons) that are not the result of an adverse event need not be considered as adverse events and are therefore not serious adverse events.

¶Routine Clinical Procedure: A procedure which may take place during the study period and should not interfere with the study product administration or any of the ongoing protocol specific procedures. If anything untoward is reported during an elective procedure, that occurrence must be reported as an adverse event or serious adverse event, according to the usual criteria.

†Disabling/incapacitating: An adverse event is incapacitating or disabling if the event results in a substantial disruption of the subject's ability to carry out normal life functions. This definition is not intended to include experiences of relatively minor medical significance such as headache, nausea, vomiting, diarrhea, influenza, and accidental trauma (eg, sprained ankle).

#### **4.2.2 Study Reporting Period for Serious Adverse Events**

The reporting period for serious adverse events is the period immediately following the first administration of study vaccine through 365 days post randomization. Serious adverse events must be followed until resolution by the investigator, even if this extends beyond the study reporting period. Resolution of a serious adverse event is defined as the return to baseline status or stabilization of the condition with the expectation that it will remain chronic.

At any time after completion of the study, if an investigator becomes aware of a serious adverse event that is suspected by the investigator to be related to study product, the event should be reported to MedImmune Product Safety.

#### **4.2.3 Notification of Sponsor of Serious Adverse Events**

**Within 24 hours of identifying a serious adverse event, regardless of the presumed relationship to the study product, the investigator must complete the SERIOUS ADVERSE EVENT (SAE) report form and fax it to MedImmune Product Safety (or designee).**

Note: Provide all available SAE information at the time of form completion. When additional information becomes available, the investigator will submit a follow-up SAE Report Form via fax to MedImmune Product Safety

MedImmune contact information:

Product Safety  
MedImmune

[figure not shown]

Fax:

[figure not shown]

MedImmune, as sponsor of the study being conducted under an Investigational New Drug Application (IND), is responsible for reporting certain serious adverse events as IND safety reports to the FDA, other applicable regulatory authorities, and participating investigators, in accordance with the U.S. Code of Federal Regulations (21 CFR 312.32 and 312.33), ICH Guidelines, and/or local regulatory requirements. MedImmune may be required to report certain serious adverse events to regulatory authorities within 7 calendar days of being notified about the event; therefore, it is important that investigators submit additional information requested by MedImmune as soon as it becomes available.

#### **4.2.4 Notification of Institutional Review Board or Independent Ethics Committee of Serious Adverse Events**

The investigator must comply with the applicable regulatory requirements related to the reporting of serious adverse events to the Institutional Review Board or Independent Ethics Committee. The Institutional Review Board or Independent Ethics Committee must be informed in a timely manner by the principal investigator of serious adverse events occurring at their site during the study. Investigators must also submit safety information provided by MedImmune to the Institutional Review Board or Independent Ethics Committee as detailed in Section 7.2.

#### **4.2.5 Recording of Serious Adverse Events**

Serious adverse events will be recorded on the Serious Adverse Event (SAE) Report Form using a recognized medical term or diagnosis that accurately reflects the event. Serious adverse events will be assessed by the investigator for severity, relationship to the study product and possible etiologies. See Sections 4.3 and 4.4 regarding guidelines for assessment of severity and relationship, respectively. For the purposes of study analysis, if the event has not resolved at the end of the study reporting period it will be documented as ongoing on the Adverse Event Case Report Form. For purposes of regulatory safety monitoring the investigator is required to follow

the event to resolution and report to the sponsor the outcome of the event using the Serious Adverse Event (SAE) Report Form.

### 4.3 Assessment of Severity

Assessment of severity is one of the responsibilities of the investigator in the evaluation of solicited symptoms, AEs, and SAEs. The determination of severity should be made by a health care professional who is qualified to review adverse event information, provide a medical evaluation of adverse events, and classify adverse events based upon medical judgment and the severity categories of *Grade 1 (Mild)*, *Grade 2 (Moderate)*, *Grade 3 (Severe)*, and *Grade 4 (Potentially Life Threatening)* as provided in [APPENDIX A](#) and [APPENDIX B](#).

### 4.4 Assessment of Relationship

The investigator is required to provide an assessment of relationship of solicited symptoms, AEs, MA-LRIs, SNMCs, and SAEs to the study product. A number of factors should be considered in making this assessment including: 1) the temporal relationship of the event to the administration of study product; 2) whether an alternative etiology has been identified; and 3) biological plausibility. The following guidelines should be used by investigators to assess the relationship of an adverse event to study product administration.

#### Relationship assessments that indicate an “Unlikely Relationship” to study product:

*None:* The event is related to an etiology other than the study product (the alternative etiology must be documented in the study subject’s medical record).

*Remote:* The event is unlikely to be related to the study product and likely to be related to factors other than study product.

#### Relationship assessments that indicate a “Likely Relationship” to study product:

*Possible:* There is an association between the event and the administration of the study product and there is a plausible mechanism for the event to be related to study product; but there may also be alternative etiology, such as characteristics of the subject’s clinical status or underlying disease.

*Probable:* There is an association between the event and the administration of study product, a plausible mechanism for the event to be related to the study product and the event could not be reasonably explained by known characteristics of the subject’s clinical status or an alternative etiology is not apparent.

*Definite:* There is an association between the event and the administration of study product, a plausible mechanism for the event to be related to the study product and causes other than the study product have been ruled out and/or the event re-appeared on re-exposure to the study product.

#### **4.5 Other Events Requiring Immediate Reporting**

In addition to SAEs, the following immediately reportable events (IREs) must be entered into the appropriate CRF page by the investigator *within 24 hours*:

1. Any withdrawal of consent during the study after the subject is randomized
2. Any Grade 3 or Grade 4 AE
3. Any MA-LRI (see Section 4.1.3 and [APPENDIX C](#) for definition)
4. Permanent discontinuation of study vaccine administration

Note: The investigator is responsible for completing the Safety Fax Notification/IRE Report Form and faxing it to MedImmune Product Safety within 24 hours.

#### **4.6 Safety Management During the Study**

The MedImmune Medical Monitor has primary responsibility for the ongoing medical review of safety data throughout the study. This includes immediate review of SAEs, MA-LRIs, and Grade 3/Grade 4 AEs, which are all immediately reportable events, and timely review of other AEs reported during the study. Monthly data listings of preliminary safety data will be provided for review of events occurring within 28 days of any study dose. The Medical Monitor will determine if the threshold has been met for immediate review of Grade 3/Grade 4 AEs (see Section 4.8), SAEs, and MA-LRIs by the Unblinded Safety Physician and Safety Biostatistician (a clinical trial specialist and statistician not directly associated with the conduct of the study). Once the threshold has been met for review of an event(s), the Unblinded Safety Physician and Safety Biostatistician have primary responsibility for assessment of Grade 3/Grade 4 AEs, MA-LRIs, and SAEs to determine whether stopping rules have been met such that events must be reviewed by the SMC (see below). At their discretion, they may review blinded or unblinded data in listings or tables, including virology data.

Consistent with protocol Section 4.1.6 (Study Reporting Period for Enhanced Disease Surveillance), the Medical Monitor has responsibility for ongoing review of MA-LRI events through 365 days post dosing to assess the need for review by the Unblinded Physician and Safety Biostatistician. For this purpose, all MA-LRI hospitalizations or deaths (whether occurring within or later than 28 days post dosing) will be attributed, hypothetically, to the vaccine arm, and if this would result in a statistical imbalance in these events, the Unblinded Physician and Safety

Biostatistician will review events in blinded or unblinded fashion in conjunction with RSV testing and event severity data to determine if imbalance has occurred. The Medical Monitor can also request review by the Unblinded Physician and Safety Biostatistician if concerns arise regarding potential imbalance in rates of MA-LRI events or severity of MA-LRI events.

If statistical imbalance in all MA-LRI hospitalizations or deaths through 365 days after randomization has occurred or if otherwise requested by the Unblinded Safety Physician and Safety Statistician, the SMC will review all MA-LRI events for a decision regarding stopping enrollment temporarily to gather additional information, stopping enrollment permanently, or amending protocol and informed consent to follow subjects through an additional RSV season.

The Medical Monitor also has the responsibility of reviewing safety data prior to initiation of Cohort 2 dosing and after enrollment of the first 40 subjects in Cohort 2 (see Section 4.9).

The MedImmune Product Safety Specialist has responsibility for the receipt, review, investigation, and follow-up of SAEs reported by the clinical study sites.

The SMC is composed of at least two MedImmune physicians who are not directly involved in the day-to-day operations of the study, and at least two physicians who are not employees of MedImmune. The SMC will independently review cumulative safety surveillance data prior to initiation of Cohort 2 dosing and after enrollment of the first 40 subjects in Cohort 2 (see Section 4.9). The SMC will also review safety data at other times in response to SAEs, MA-LRIs, Grade 3/Grade 4 AEs, or other AEs considered medically significant by the Medical Monitor or the Unblinded Safety Physician and Safety Biostatistician (see Section 4.8). Additionally, the SMC reviews immediately reportable events monthly. The SMC will review the data in a treatment blinded or unblinded manner and determine whether randomization and/or dosing should be discontinued. SMC review is required for resumption of the study in the event that study randomization and/or dosing are stopped according to stopping rules in Section 4.8. Additionally, the SMC will review decisions of the Medical Monitor and the Unblinded Safety Physician and Safety Biostatistician regarding study vaccination on a regular basis throughout the study. When SMC decisions regarding discontinuation or resumption of dosing and/or randomization are made, these decisions will be communicated promptly to the FDA and to other regulatory authorities as applicable.

The SMC conducts all safety assessment independently of the Medical Monitor. Closed sessions are held as necessary to review blinded data and to reach consensus without the presence of the Medical Monitor. The SMC decision is the final decision and supersedes the assessment of the Medical Monitor or Unblinded Safety Physician and Biostatistician.

#### **4.7 Interruption or Discontinuation of Study Dosing in Individual Subjects**

An individual subject will not receive a scheduled study vaccine dose if any of the following occur in the subject in question. The subject may be vaccinated at a later date *upon resolution* of the event provided that vaccination occurs within the protocol-specified vaccination window.

1. Any fever ( $\geq 100.4^{\circ}\text{F}$  [ $\geq 38.0^{\circ}\text{C}$ ]), regardless of route, at the time of study vaccine administration
2. Acute illness at time of study vaccine administration (acute illness is defined as the presence of moderate or severe signs and symptoms)
3. Moderate or severe nasal congestion that in the investigator's opinion could prevent intranasal delivery of the study vaccine

An individual subject will not receive a scheduled study vaccine dose if any of the following occur in the subject in question. The subject may be vaccinated at a later date provided that vaccination occurs within the protocol-specified vaccination window.

1. Receipt of any live virus vaccine (excluding rotavirus vaccine) within 28 days prior to vaccination or expected receipt within a 28 day window around any dose
2. Receipt of any inactivated (eg, non-live) vaccine or rotavirus vaccine within 14 days prior to vaccination or expected receipt within a 14 day window around any dose
3. Recent use or expected receipt of immunosuppressive agents including steroids ( $\geq 2$  mg/kg per day of prednisone or its equivalent, or  $\geq 20$  mg/day if the subject weighs  $>10$  kg, given daily or on alternate days for  $\geq 14$  days); children in this category should not receive study vaccine until immunosuppressive agents including corticosteroid therapy have been discontinued for  $\geq 30$  days
4. Living in the same home or enrolled in the same classroom at full-time day care with infants  $<6$  months of age within 28 days after each dose
5. Contact with pregnant caregiver within 28 days after each dose
6. Living in a household with someone who is immunocompromised within 28 days after each dose; the subject should also avoid close contact with immunocompromised individuals for 28 days after each dose
7. Living in a household with someone who works in the healthcare field and who has direct patient care responsibilities within 28 days after each dose
8. Living in a household with someone who is a day care provider or preschool teacher for children  $<6$  months of age within 28 days after each dose
9. Any condition that, in the opinion of the investigator, might interfere with study vaccine evaluation

If a subject does not receive study vaccine during the Dose 2 vaccination window, the subject may receive study vaccine in the Dose 3 vaccination window, if eligible. If Dose 2 is missed, the Dose 3 vaccination window will be 96 to 120 days post Dose 1. Unless consent is withdrawn, subjects who receive 1, 2, or 3 doses of study vaccine will be followed for the full study period through 365 days post randomization, including the collection of any protocol-specified samples (final blood sample and nasal wash samples in accordance with [APPENDIX C](#)). Subjects who miss a dose of vaccine will not have the post-dose study visits and nasal washes performed. Subjects who have dosing interrupted in accordance with Section 4.7 (Interruption or Discontinuation of Study Dosing in Individual Subjects) and who are expected to receive a subsequent dose of vaccine will not have blood obtained after dosing. Subjects who have study vaccine permanently discontinued (see Subsection, Permanent Discontinuation of Study Vaccine) should have a study visit to obtain a final post-dosing blood sample 28 to 34 days post last dose or within 4 weeks of the decision to discontinue all dosing. For all subjects, unscheduled visits to obtain illness nasal washes must be held in accordance with APPENDIX C.

### **Permanent Discontinuation of Study Vaccine**

An individual subject will not receive any further study vaccine if any of the following occur in the subject in question:

1. Withdrawal of consent
2. Acute allergic reaction (consistent with a significant IgE mediated event) or anaphylaxis following the administration of a previous dose
3. Any respiratory SAE
4. Any SAE assessed as related (possibly, probably, or definitely) to study vaccine
5. Use of any investigational or non-registered drug or vaccine product since the previous dose administration
6. Intercurrent history of receipt of blood transfusion or expected receipt through 28 days following final study vaccine dosing
7. Intercurrent history of receipt of immunoglobulin products or expected receipt through 28 days after final study vaccine dosing
8. Event which in the opinion of the investigator or Medical Monitor contraindicates further dosing such as illnesses or complications
9. Noncompliance with protocol that, in the opinion of the investigator or sponsor, limits the ability to follow the subject for safety or to obtain trial data
10. Termination of research by sponsor or investigator
11. Known or suspected immunodeficiency including HIV

Unless consent is withdrawn, subjects who are permanently discontinued from study vaccine will be followed (including the collection of all protocol-specified samples) for the full study period (through 365 days after randomization). Subjects who are permanently discontinued from study vaccine should have a blood sample obtained 28 to 34 days post last dose or as soon as possible once the decision is made to discontinue all dosing, and visits to obtain illness nasal washes must be held in accordance with [APPENDIX C](#).

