### **SUBJECT EVALUATION AND FOLLOW-UP:**

Safety will be evaluated by the collection of solicited symptoms, adverse events (AEs), serious adverse events (SAEs), concomitant medication use, medically attended lower respiratory illness (MA-LRI, defined in Section 4.1.3) and significant new medical conditions (SNMCs, defined in Section 4.1.4). The subject's legal representative will complete a worksheet to bring to study clinic visits to facilitate collection of potential solicited symptoms, AEs, SAEs, and concomitant medications and vaccines. AEs, and SAEs will be assessed for severity and relationship to study vaccine. Solicited symptoms will be assessed for severity and SNMCs will be assessed for relationship to study vaccine.

A nasal wash specimen will be collected at Days 7, 12, and 28 following each dose to assess vaccine virus replication and vaccine-like viral shedding. Additional unscheduled nasal wash specimens will be collected from subjects who require an unscheduled illness visit in accordance with protocol Section 3.4. All subjects who experience an MA-LRI during the entire 365 study period will be asked to return to the clinical site for a nasal wash specimen collection. Nasal wash specimens will be assayed for the presence of vaccine-like virus and for the presence of certain respiratory pathogens. All vaccine virus that is recovered from nasal wash samples will

be quantified to evaluate the level of replication as a marker of attenuation. Vaccine virus that is isolated will also be evaluated for genotypic stability.

A serum sample will be collected at the Study Day 0 visit for the baseline assessment of immune response. Subjects whose legal representative have provided written informed consent for the collection of additional samples will have 3 additional serum samples collected at the Day 7 and Day 28 visits after Dose 1 and at the Day 28 visit after Dose 2 to assess immune response. A serum sample will be obtained for all enrolled subjects 28-34 days after the final dose to assess immune response.

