**56 Days Post Dose 2 (56 ± 8 days post dosing) Dose 2: Administration of Dose 3**

*Visit 9*

1. Verify continuing eligibility
2. Update medical history
3. Perform targeted physical exam
4. Update AEs and concomitant medication use that were continuing 28 days after Dose 2  

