### **3.5.3 Immune Response Evaluations**

Two blood samples will be drawn from each subject for immunogenicity evaluation. All subjects will have blood draws for immunogenicity evaluation performed on Day 0 (prior to administration of Dose 1) and 28 days after Dose 3 (or final dose if subject prematurely terminates study dosing). Serum samples will be stored at -20°C and sent to MedImmune CTL (or a MedImmune-approved central laboratory) for immunogenicity evaluation and potential future testing.

Subjects whose legal representatives have provided written informed consent for additional sampling may have 3 additional blood draws performed for immunogenicity evaluations. Written informed consent will be obtained from the legal representative of each of these subjects prior to study entry. For subjects scheduled to have the additional blood draws performed, samples will be obtained 7 and 28 days after Dose 1 and 28 days after Dose 2.

Immune response will be evaluated by measuring functional serum antibody responses to RSV (microneutralization assay). In addition, because the immune response generated by live attenuated vaccines is poorly understood, a number of exploratory immunology assays may be conducted to guide further vaccine development. These assays may be performed according to the presence of appropriate samples and appropriate assays.

- Specific IgG and IgA antibody to RSV by investigational ELISA
- Mucosal immune responses using IgG and IgA ELISA; specific IgG and IgA will be standardized to total IgG or IgA
- Mucosal cytokine profile
- Exploratory transcription profiling (eg, mRNA microarray analysis, a tool for studying the function of genes by revealing their pattern of expression or regulation; it is not genetic testing) may be used to characterize the nature of the immune response

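### The final serum sample for seroresponse has conflicting timing rules for children who stop dosing early, and two of them allow a draw before Day 28

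*Protocol*

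**What the plan says.** Four statements in the protocol govern the same sample.

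- Study Abstract, Subject Evaluation and Follow-up: "A serum sample will be obtained for all enrolled subjects 28-34 days after the final dose to assess immune response".
- Section 3.5.3: blood at Day 0 and "28 days after Dose 3 (or final dose if subject prematurely terminates study dosing"), with no alternative.
- Section 4.7, text before the subsection on permanent discontinuation: "28 to 34 days post last dose or within 4 weeks of the decision to discontinue all dosing".
- Section 4.7, Permanent Discontinuation of Study Vaccine: "28 to 34 days post last dose or as soon as possible once the decision is made to discontinue all dosing".

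Section 4.7 also says that children whose dosing is interrupted and "who are expected to receive a subsequent dose of vaccine will not have blood obtained after dosing". Footnote k to Table 1 gives children without consent to the optional draws two blood samples only: Day 0 and 28 days after Dose 3.

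Section 5.5 defines seroresponse as a fourfold or greater increase in neutralizing titre over baseline, measured after the final dose. Neither that definition nor the immune response population in Section 5.3 carries a timing condition.

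**The concern.** The planned time for this endpoint is about Day 28 after the last dose. The two rules in Section 4.7 each join that window to a second option with a bare *or*. The second option is counted from the decision to stop, not from the dose. Several of the listed reasons for permanent discontinuation, such as an acute allergic reaction, a respiratory SAE or a related SAE, can arise within days of a dose. In such a child the protocol permits a draw well before Day 28.

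At stake is the meaning of the seroresponse percentage. A child bled early may be scored as a non-responder only because of the date of the draw. An analysis window in the SAP could exclude that sample, but it could not replace it if no later one was taken. The timing has to be right at collection, and the protocol is where collection is fixed.

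**Working it through.** The protocol states no figure to reproduce here. The check is date arithmetic on its own windows, followed by an illustration that rests on assumptions.

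**Early end.** Let the decision to stop fall on Day k after the last dose.

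- Abstract: Day 28 to 34. Section 3.5.3: Day 28.
- Section 4.7, 4-week branch: Day k to Day k + 28.
- Section 4.7, as-soon-as-possible branch: Day k onward.
- Both Section 4.7 branches therefore permit a draw before Day 28 whenever k < 28.
- For k = 5, the 4-week branch runs from Day 5 to Day 33. A draw on Day 6 satisfies both parts of Section 4.7 and falls 28 − 6 = 22 days before the earliest day in the abstract.

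The two parts of Section 4.7 can be met by one draw, so they differ in their limit and do not exclude each other. The real conflict is between both of them and the abstract and Section 3.5.3.

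**Late end.** Inputs: the Dose 3 window after Dose 2 ("56 Days Post Dose 2 (56 ± 8 days post dosing")) and the window when Dose 2 is missed ("If Dose 2 is missed, the Dose 3 vaccination window will be 96 to 120 days post Dose 1").

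- Dose 2 missed, stop decided when the Dose 3 window closes: 120 + 28 = Day 148 after Dose 1.
- Dose 3 missed, stop decided at window close: 56 + 8 = 64, then 64 + 28 = Day 92 after Dose 2. Dose 2 is given at most 64 days after Dose 1, so this is at most 64 + 92 = Day 156 after Dose 1.
- A child who follows the full schedule is bled between 48 + 48 + 28 = 124 and 64 + 64 + 34 = 162 days after Dose 1.

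Both late cases fall inside the 124 to 162 day range. Measured from the Day 0 baseline, a late draw gives no more time for wild-type infection than the schedule itself gives.

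**Possible size of the early effect (assumed).** The protocol gives no share of children who stop early. Suppose a share d of an arm of 80 is bled too early and every one of them reads as a non-responder. The observed rate is then p × (1 − d). The values of p are the neutralizing responses that Section 1.4 quotes for the predecessor vaccine at its higher dose: 88% in seronegative children (8 children) and 19% in young infants.

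| d (children of 80) | p = 88%, like Cohort 1 | p = 19%, like Cohort 2 |
|---|---|---|
| 5% (4) | 83.6% | 18.1% |
| 10% (8) | 79.2% | 17.1% |
| 20% (16) | 70.4% | 15.2% |

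For a given d these are upper limits on the loss. A child stopped on Day 5 after Dose 2 is at least 48 + 5 = 53 days past Dose 1 and may already show a rise.

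**The case against.** The strongest reply is that both rules in Section 4.7 begin with Day 28-34, so the second branch is naturally a fallback for when that window has gone by. Blood is withheld while a further dose is expected, which makes such a fallback necessary, and Section 3.5.3 supports this reading. On that view nobody would be bled on Day 6. The reading is sensible and may be what was meant, but the text does not say it, and a site that bled on Day 6 would have followed Section 4.7.

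A second reply is that sample windows belong in the SAP, which is not shown. That holds for the analysis: the missing timing condition in Sections 5.3 and 5.5 is not itself a fault, and the protocol does not say that an early sample must count. It does not hold for collection.

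A reader might infer more than the documents support:

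- *That late draws bias the result, through wild-type infection or waning.* The exposure argument fails on the 124 to 162 day comparison. The protocol gives no waning figure. Days 148 and 156 also treat a closed dose window as a decision to discontinue, which is not among the listed criteria.
- *That an early draw precedes any possible response.* The protocol gives no time of antibody onset.
- *That the error differs by arm.* No discontinuation rates by arm are given, so this is conjecture.

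**Conclusion.** The inconsistency is real and limited. The abstract and Section 3.5.3 fix the final serum at Day 28-34, or Day 28, after the final dose. Both parts of Section 4.7 add an alternative with no order of priority and no Day 28 floor. Read literally, a child who stops within days of a dose, without consent to the optional draws, may have the only post-dose sample taken well before the planned time. That may understate seroresponse.

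Only children permanently discontinued before Day 28 after a dose are exposed to this. Their number is unknown and probably small. The tabled losses depend wholly on the assumed shares and on scoring every early sample as a non-response, so they are not estimates. The endpoint is secondary and descriptive, no formal tests are planned, and no primary endpoint is touched. The point merits correction because an early sample cannot be put right afterwards and the correction is cheap.

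There is also a plain gap. A child who simply misses the Dose 3 window and meets no discontinuation criterion is left with the Day 28 or Day 28-34 rule alone, and that time has passed before the window opens on Day 48 after Dose 2.

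**What to change.** Put one rule in the abstract, Section 3.5.3 and both parts of Section 4.7:

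- Draw the final blood 28-34 days after the last dose received, and not before Day 28.
- Only if Day 34 has already passed when it is settled that no further dose will be given, draw it as soon as possible and within 4 weeks of that decision. State that this includes a dose window that closes without a dose.

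In the analysis, flag samples outside Day 28-34 and report seroresponse with and without them. The flag can sit in the SAP.

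The cost is a wording change in an amendment and one timing flag, with no added draw. A few children who stop early would wait until Day 28 for a sample they are due anyway, and some may be lost before it. The late fallback does not shorten the interval for children whose window has passed; it only gives them a rule that can be met.
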